**Abstract**

***Introduction***

Depression is a leading mental health problem worldwide. People with long-term conditions are at increased risk of experiencing depression. The COVID-19 pandemic led to strict social restrictions being imposed across the UK population. Social isolation can have negative consequences on the physical and mental wellbeing of older adults. In the Behavioural Activation in Social IsoLation (BASIL^+^) trial we will test whether a brief psychological intervention (based on Behavioural Activation), delivered remotely, can mitigate depression and loneliness in older adults with long-term conditions during isolation.

***Methods***

We will conduct a two-arm, parallel-group, randomised controlled trial across several research sites, to evaluate the clinical and cost-effectiveness of the BASIL^+^ intervention. Participants will be recruited via participating general practices across England and Wales. Participants must be aged ≥65 with two or more long-term conditions, or a condition that may indicate they are within a ‘clinically extremely vulnerable’ group in relation to COVID-19, and have scored ≥5 on the Patient Health Questionnaire (PHQ9), to be eligible for inclusion. Randomisation will be 1:1, stratified by research site. Intervention participants will receive up to eight intervention sessions delivered remotely by trained BASIL^+^ Support Workers and supported by a self-help booklet. Control participants will receive usual care, with additional signposting to reputable sources of self-help and information, including advice on keeping mentally and physically well.

A qualitative process evaluation will also be undertaken to explore the acceptability of the BASIL^+^ intervention, as well as barriers and enablers to integrating the intervention into participants’ existing health and care support, and the impact of the intervention on participants’ mood and general wellbeing in the context of the COVID-19 restrictions. Semi-structured interviews will be conducted with intervention participants, participant’s caregivers/supportive others and BASIL^+^ Support Workers.

Outcome data will be collected at one, three, and 12 months post-randomisation. Clinical and cost-effectiveness will be evaluated. The primary outcome is depressive symptoms at the three-month follow up, measured by the PHQ9. Secondary outcomes include loneliness, social isolation, anxiety, quality of life, and a bespoke health services use questionnaire.

***Discussion***

This study is the first large-scale trial evaluating a brief Behavioural Activation intervention in this population, and builds upon the results of a successful external pilot trial.

***Trial Registration***  ClinicalTrials.Gov identifier ISRCTN63034289, registered on 5th February 2021.

***Funding***

This study was funded by National Institute for Health Research (NIHR) Programme Grants for Applied Research (PGfAR) RP-PG-0217-20006

**Introduction**

Long-term health conditions (LTCs) are reported to be more prevalent in older people, and numbers continue to increase. This includes the number of older people with multiple LTCs [1]. The co-existence of two or more chronic conditions is termed ‘multiple long-term conditions’ (MLTCs) by the National Institute for Health Research (NIHR) [2]. NICE guidance highlights the importance of individualised treatment plans that address both physical and psychological conditions [3].

Depression is a major contributor to the overall global burden of disease according to the World Health Organisation [4] and is set to become the highest among all health problems by 2030 [5]. A two-to-three-fold increase in the prevalence of depression is found across the range of LTCs, resulting in poorer outcomes, lower quality of life and increased mortality [6]. Additionally, people with depression are more likely to have two or more LTCs and experience the greatest reduction in quality of life [7]. This results in substantially increased treatment costs and a significant contribution to health inequalities, particularly among older adults [8].

The Coronavirus 2 (SARS-CoV-2) virus (and the COVID-19 disease it causes) reached pandemic status in March 2020 triggering a national Stay At Home order (“lockdown”), where the UK government and devolved nations instructed individuals to follow compulsory social distancing and self-isolation rules. In addition, more than 2.2 million people were identified by the NHS as ‘clinically extremely vulnerable’ (including those with specific health conditions and older people) and were advised to follow stricter forms of isolation (“shielding”) [9]. Restriction levels have varied throughout the pandemic, with many people choosing to continue shielding, or maintain previous social distancing guidance, regardless of restrictions being eased [10].

The population’s mental health has worsened as a consequence of the pandemic [11], with reports of an increase in feelings of depression, anxiety and loneliness in older adults [12]. The social restrictions imposed to attempt to contain the virus led to widespread social and economic disruption. This rapid change to social norms increased isolation leading to loneliness and depression, which are known factors in the development of poorer mental health outcomes [12]. Existing research supports these reports, highlighting how social isolation has a disproportionate effect on the physical and mental wellbeing of older adults [13, 14]. Loneliness is also considered a significant public health concern in those aged 60 years and over, with evidence showing a link between persistent loneliness and increased healthcare utilisation, regardless of health status [13]. Furthermore, a longitudinal study of ageing indicated loneliness is linked to future depression, as depressive symptoms increased over time among people with higher loneliness scores [15]. Loneliness is not an inevitable consequence of social isolation, and approaches to mitigate loneliness were highlighted as population priority even before the COVID-19 pandemic [16, 17]. Such approaches include focusing on social networks [18] or adapting strategies derived from cognitive behavioural therapy in order to maintain social connectedness [19]. This emphasises the need for an intervention incorporating both depression and loneliness, which could potentially mitigate the immediate and longer lasting psychological impacts of COVID-19 on vulnerable populations, including older people and those with LTCs [20].

Behavioural Activation (BA) is a clinically effective structured psychological treatment for depression, encouraging individuals to reconnect with valued activities and positive reinforcement in their environment [21]. The therapist (or ‘case manager’) and patient work together to reinstate (or replace, if former activities are no longer possible) behaviours that improve mood and encourage the patient to remain active. It has the potential to address the disrupted routines and reduced opportunities for physical activity and social contact that have resulted from the increased social isolation older adults have faced over the course of the pandemic, whilst also addressing the social isolation that some older adults may have faced irrespective of the pandemic. BA is delivered within a Collaborative Care framework, which is a way of organising care so that an intervention is delivered in the most effective, patient-centred way. A Cochrane review has emphasised the importance of Collaborative Care in relation to multiple long-term conditions [22]. Evidence supports Collaborative Care for people with depression particularly if it includes a structured psychological intervention [22]. Given the nature of the COVID-19 pandemic, it is crucial that such interventions are able to be delivered remotely. Evidence suggests it is feasible and acceptable to use remote interventions to mitigate the psychosocial consequences (including depression and loneliness) of COVID-19 [23].

Recent research has described the impacts of the pandemic on the population’s mental health [24, 25]. However, clinical trials to test interventions to prevent and alleviate the psychological impact of COVID-19 have been limited, with drug and vaccine development trials prioritised [26]. By late 2019, we had co-developed a brief and scalable psychological intervention (based on BA) as part of an existing programme of work (Multi-Morbidity in Older Adults with Depression Study, MODS (RP-PG-0217-20006)). The MODS intervention was designed to be delivered mostly by telephone (with a face to face contact for the first session) for older adults with MLTCs and depression. Plans to test the MODS intervention were halted in March 2020 due to the pandemic. In response to the pandemic and in an effort to mitigate the psychological impacts of social isolation on older adults with long-term health conditions, we drew on the accumulated knowledge from MODS to adapt the MODS BA intervention to facilitate remote delivery – and developed the BASIL (Behavioural Activation for Social IsoLation) programme of work.

An external pilot Randomised Controlled Trial (RCT) commenced in April 2020 (BASIL-C19) to test the feasibility and acceptability of the BASIL intervention and remote trial delivery. The pilot study indicated that BA was a plausible intervention to mitigate the psychological impacts of COVID-19 isolation for older adults and is acceptable and feasibly delivered remotely [23]. The clinical and cost-effectiveness of the BASIL intervention will now be tested in a fully-powered large-scale RCT (BASIL+).

**Materials and Methods**

***Research Aims***

The aim of the BASIL^+^ trial is to test the clinical and cost-effectiveness of a brief psychological intervention (BA) with embedded process and economic evaluations:

- Establish the clinical effectiveness of BA in preventing and mitigating depression and loneliness among older people with multimorbidity during isolation.
- Establish the cost effectiveness of BA in preventing and mitigating depression and loneliness among older people with multimorbidity during isolation.
- To explore barriers and facilitators to implementation, in healthcare services, of the BA intervention for older people with multiple LTCs during isolation.

***Design***

The BASIL^+^ trial is a two arm, parallel-group, multicentre, randomised controlled trial with embedded qualitative process and economic evaluations. The trial also includes a methodological Study Within a Trial (SWAT) to evaluate the impact of a study infographic on participant recruitment and response rates. The schedule of enrolment, interventions and assessments is shown in Figure 1.

***Setting***

Participants will be identified via general practices across England and Wales. The intervention will be delivered across a range of health care settings (e.g. primary care, secondary care, voluntary/third sector).

***Identification***

Potential participants will be identified via searches of patient registers at general practices. Lists of patients aged 65 and over with two or more long-term conditions (LTCs) or a condition that may indicate they are ‘clinically extremely vulnerable’ in relation to COVID-19 (following UK Health Security Agency (UKHSA), previously known as Public Health England guidance) will be generated. Patient lists will be screened by General practitioner (GP) practice teams to remove patients meeting exclusion criteria (detailed below).

LTCs will be based on the Department of Health (DoH) definition [27]. We will primarily focus on commonly reported LTCs for older people (such as asthma/ chronic obstructive pulmonary disease, diabetes, hypertension/coronary heart disease, and stroke) according to the primary care Quality and Outcomes Framework (QOF) [28] but will also include conditions such as musculoskeletal problems and chronic pain.

***Inclusion Criteria:***

- Older adults (65 years or over)
- Two or more long-term conditions (LTCs) or a condition that may suggest they are within a ‘clinically extremely vulnerable’ group in relation to COVID-19
- A score of ≥5 at screening on the Patient Health Questionnaire (PHQ9) (a score of 5-9 indicates possible sub-threshold depression, 10 and above indicates possible depression) [29]

***Exclusion Criteria:***

- Cognitive impairment
- Bipolar disorder/psychosis/psychotic symptoms
- Alcohol or drug dependence
- In the palliative phase of illness
- Have active suicidal ideation
- Currently receiving psychological therapy
- Unable to speak or understand English

Older adults will not be excluded on the basis of living in residential/care homes.

***Recruitment***

Identified potential participants will receive a study information pack (containing a practice letter-headed invitation letter, Participant Information Sheet and an example consent form) and a text message about BASIL^+^ (where possible) via their GP practice. Patients will be given the option to complete an online consent form (via a link provided in the PIS, mirroring the example consent form patients receive), or to contact the study team directly. Extended GP practice teams will contact the remaining potential participants by telephone to determine interest in the study. Verbal permission to pass on their contact details (permission to contact (PTC)) to the local BASIL^+^ study team will be obtained from interested patients and recorded.

A BASIL^+^ study researcher will then make contact via telephone (or video call using an appropriate online platform) to discuss the study, answer any questions and determine eligibility. Where patients are eligible and wish to participate, informed consent will be obtained (where online consent has not already been provided). In response to the need to deliver the trial remotely, the informed consent process will involve taking consent verbally. Participants will be directed to the example consent form provided in the study information pack; the a researcher will read out each of the consent statements, and request that the participant respond to confirm whether they agree or disagree with the statement, and creating a written record of their responses. Once informed consent has been confirmed, the baseline questionnaire will then be completed over the telephone with a researcher (either immediately following confirmation of eligibility or at a later date, in line with participant preference, and ideally within one week).

***Randomisation and blinding***

Following baseline questionnaire completion, eligible and consenting participants will be randomised 1:1 to either receive the intervention (BA) or usual care with signposting information. Randomisation will take place via a secure online randomisation service provided by the York Trials Unit (YTU). A YTU statistician not involved with participant recruitment will generate the allocation schedule, using block randomisation stratified by site with randomly varying block sizes. Participants will be informed of their group allocation by telephone (and confirmed by letter). The participant’s GP will be informed by letter of the participant’s group allocation; this will include information about the participant’s mood symptoms (with the participant’s consent).

Researchers completing follow-up questionnaires (outcome measures) with participants over the telephone will be blind to group allocation. Due to the nature of the intervention, it is not possible to keep participants or the BASIL^+^ Support Workers delivering the intervention blind to allocation.

***Intervention***

***BASIL^+^ intervention***

The BASIL^+^ intervention uses BA set within a Collaborative Care framework. BA aims to help people stay connected with the world by helping them to maintain activities which they value. Where valued activities may no longer be possible, either in the short or long-term, BA prompts participants to think about alternative activities which fulfil a similar function and help them to remain active. Remaining active and staying connected with the world may benefit physical and emotional wellbeing, which could be particularly important where COVID-19 restrictions have disrupted usual routines and connections with the outside world. The BASIL Support Worker (BSW) and the participant will work together using a self-help workbook to develop an individualised treatment plan. The plan will take into account relevant COVID-19 guidance and aid in the establishment of new daily routines. Support will be provided to help participants use technology to maintain contact with those important to them or access services. The booklet also recognises that participants may be worried about the current situation due to COVID-19, either about the pandemic itself or recommencing activities they have not undertaken for some time. The BSW can work with the participant to identify simple strategies to manage worry and help them to recommence activities in a way which makes them feel most comfortable.

The Collaborative Care aspect of the intervention may involve the BSW supporting the participant to take a proactive role in managing their mood and long-term health conditions. The BSW will liaise with the participant’s GP or other professionals involved in the participant’s care, if appropriate. They may also provide information about relevant support services or organisations running activities relevant to the participant’s interests.

Participants will be offered up to eight intervention sessions, delivered by a trained BSW and supported by the self-help booklet. The self-help booklet has been developed over a number of similar studies; most recently during the BASIL-C19 pilot study [23], where it was adapted for use during the COVID-19 pandemic with help and feedback from older adults, BSWs and a range of stakeholders, including members of the existing MODS/BASIL Patient and Public Involvement (PPI) group. Further minor adaptations were made for BASIL^+^ following the BASIL-C19 pilot (including minor design and wording changes to the self-help booklet). All sessions will be delivered remotely, either over the telephone or by video call (where this is available and preferred) and according to participant preference. The first session will last approximately one hour with subsequent sessions lasting approximately 30 minutes.

The depression scale of the Depression Anxiety Stress Scale (DASS) [30] will be used as a within session depression symptom monitoring tool. The DASS is a widely used and simple to score monitoring tool with clear clinical cut off scores (non/mild/moderate/severe). DASS scores will be used to aid decision making by BSWs in conjunction with their BASIL^+^ clinical supervisor. Where risk or significant clinical deterioration is indicated the participant will be supported to access more formal healthcare interventions.

***BASIL^+^ Support Workers (BSWs)***

BSWs will have a range of backgrounds (clinical and non-clinical). They will be required to complete bespoke intervention training (approximately 22 hours) facilitated by clinical members of the study team. Materials, including recorded presentations, role-play demonstration of sessions and a support worker treatment manual will be provided to the BSWs prior to three, two-hour online/video group training sessions. The training will cover the components of the BA intervention within the Collaborative Care framework, intervention delivery, and study procedures. BSWs will be required to pass a telephone-based bespoke competency assessment with a training facilitator before commencing delivery of the intervention. BSWs will receive regular supervision/support from a clinical member of the BASIL^+^ study team.

***Comparator***

Participants allocated to the usual care with signposting information group will receive their usual care as provided by their current NHS and/or third sector providers. In addition, usual care (control) participants will be signposted to sources of self-help and information, including advice on how to keep mentally and physically well. Examples of such sources includes guidance from UK Health Security Agency (UKHSA), previously known as Public Health England [31], and Age UK [32].

***Outcome measures***

Data will be obtained at baseline and one, three, and twelve months post-randomisation. Baseline data will be collected over the telephone with a researcher. Participants will be offered the option to complete follow-up questionnaires online, via a secure emailed link, or over the telephone with a researcher. A reminder system including emails and letters will be in place to use where appropriate.

The primary outcome will be self-reported depression severity (as measured by the PHQ9) [29] at three months post-randomisation.

Secondary outcomes will include depression (PHQ9) [28] at one and twelve months, and loneliness (De Jong Gierveld Scale – 11 items) [33]; social isolation (Lubben Social Network Scale - 6 items) [34]; anxiety (GAD7) [35]; and health related quality of life (SF-12v2 [36] and EQ-5D-3L [37]) at one, three and twelve months post-randomisation. A bespoke questionnaire will be used to collect health service use data at all time-points. Information regarding COVID-19 circumstances will be collected at all-time points.

Demographic information will be collected at baseline, to include age, LTC types/health condition(s), socio-economic status, ethnicity, education, cohabitation status, number of children.

***Data management plan***

Data will be securely stored on University or NHS computers and in secure settings. For those research staff working remotely, these servers will be accessed through secure organisation VPNs. Where data will be stored at non-NHS sites, the process for secure data storage will be reviewed and approved by the trial Sponsor. All data will be stored securely in line with GCP and GDPR guidance. Access to participant data will be restricted according to researcher role. Participant confidentiality will be maintained at all times unless significant risk to self or others is identified.

***Study Within a Trial (SWAT)***

Relying on a text-heavy PIS has become the norm for many trials. There is conflicting evidence that introducing infographics (visual representations of information) has the potential to improve the participant experience [38, 39, 40].

A methodological Study Within a Trial (SWAT) will be embedded within BASIL+ to evaluate the effectiveness of a single page infographic, to go alongside the PIS, on participant recruitment and response rates. The infographic displays a participant’s journey through the BASIL^+^ trial. The use of the infographic will be tested in a cluster RCT embedded within the BASIL^+^ trial. Study sites (n=12 approx.) will be randomised 1:1 using simple randomisation to either the SWAT intervention group (potential participants receive PIS as usual, and infographic) or the SWAT control group (potential participants receive PIS as usual, and no infographic). Generation of the SWAT allocation sequence will be undertaken independently by a statistician at YTU not involved with the BASIL^+^ recruitment process. Study sites will be blind to SWAT group allocation.

The primary outcome of the embedded SWAT will be the participant recruitment rate into the BASIL^+^ trial. Secondary outcomes will be i) participant response rate in terms of expressions of interest in BASIL+ (permission to contacts received, direct participant contacts, or participant completion of the online consent form – see recruitment section above), and ii) retention in BASIL+ as measured by response to the three month post-randomisation participant questionnaire.

The proportion of participants randomised into the BASIL^+^ trial will be compared between the SWAT groups using a logistic regression model, adjusting for trial site as a random effect. The secondary outcomes will be similarly analysed; the model for response rate at the three-month follow-up will also include a covariate for BASIL+ allocation (intervention/usual care/not randomised). A simple cost analysis will be conducted to estimate the cost per extra participant recruited associated with the infographic.

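### Simple randomisation of about 12 SWAT sites is valid, but leaves a 39% chance of a 4:8 or worse split that restricted allocation would avoid at almost no cost

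*Protocol*

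**What the plan says.** The Study Within a Trial (SWAT) section makes the site the unit of randomisation: "The use of the infographic will be tested in a cluster RCT embedded within the BASIL^+^ trial". Sites receive the information sheet either with or without a one-page infographic. The allocation method is fixed there: "Study sites (n=12 approx.) will be randomised 1:1 using simple randomisation". The section names no restriction on that draw.

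Two safeguards are stated. On the sequence: "Generation of the SWAT allocation sequence will be undertaken independently by a statistician at YTU not involved with the BASIL^+^ recruitment process". On masking: "Study sites will be blind to SWAT group allocation".

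The SWAT primary outcome is recruitment into BASIL+. It is compared between the SWAT groups "using a logistic regression model, adjusting for trial site as a random effect". No power, effect size or intracluster correlation is given for the SWAT.

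For the host trial, the Randomisation and blinding section has the same trials unit allocate participants "using block randomisation stratified by site with randomly varying block sizes".

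**The concern.** Simple randomisation is in effect a separate coin toss for each site. With hundreds of units the resulting imbalance is negligible, but with about 12 it is not. Site enters the SWAT analysis as a random effect, so the precision of the recruitment comparison depends heavily on how many sites fall in each arm. An arm of three or four sites estimates its recruitment rate poorly and leans heavily on each of them.

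The stake is the precision of the SWAT's primary outcome. The loss is avoidable, because the split can be controlled when the list is generated without recruiting anyone else.

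**Working it through.** **Inputs.** About 12 sites, each with probability 0.5 of either arm (SWAT section). The protocol states no SWAT sample size or imbalance probability, so there is no figure of its own to reproduce.

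**Probability of each split.** With N = 12, P(k sites in one given arm) = C(12, k) / 2^12, and 2^12 = 4096. Both directions are added for unequal splits.

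**Variance cost.** Assume sites of similar size and dominant between-site variation. The variance of the difference is then proportional to 1/a + 1/b for an a:b split. Relative to 6:6 the factor is (1/a + 1/b) / (1/6 + 1/6). For example, 4:8 gives (0.25 + 0.125) / 0.3333 = 1.125.

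| Split | Count of 4096 | Probability | Variance factor |
|---|---|---|---|
| 6:6 | 924 | 22.6% | 1.00 |
| 5:7 | 1584 | 38.7% | 1.03 |
| 4:8 | 990 | 24.2% | 1.125 |
| 3:9 | 440 | 10.7% | 1.33 |
| 2:10 | 132 | 3.2% | 1.80 |
| 1:11 | 24 | 0.6% | 3.27 |
| 0:12 | 2 | 0.05% | not estimable |

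**Tails.**
- 4:8 or worse: (990 + 440 + 132 + 24 + 2) / 4096 = 1588 / 4096 = 38.8%.
- 3:9 or worse: 598 / 4096 = 14.6%.
- 2:10 or worse: 158 / 4096 = 3.9%.

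**Average cost.** Weighting the factors by their probabilities, given at least one site in each arm, yields a mean of 1.116. That is about 12% on the variance, or about 6% on the standard error (√1.116 = 1.056).

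**Sensitivity to the approximate site number.** For N = 10, 11, 12, 13 and 14, the probability that the arms differ by four or more sites is 34.4%, 22.7%, 38.8%, 26.7% and 42.4%. The mean variance factor is 1.15, 1.13, 1.12, 1.10 and 1.09. With an odd number of sites, a difference of four or more means at least five, which is why those probabilities are lower.

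**Illustration in power.** The protocol gives none, so assume 80% power at 6:6, a two-sided 5% test and a t comparison of 12 site-level summaries on 10 degrees of freedom. Power is then 78.9% at 5:7, 75.3% at 4:8, 68.1% at 3:9 and 55.3% at 2:10. The average under simple randomisation is about 76%.

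**Under a restricted draw.** Choosing 6 of 12 sites at random gives 6:6 every time and a variance factor of 1.00. It still leaves C(12, 6) = 924 possible allocations.

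**The case against.** Several points on the other side stand and limit the finding.

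- **The ratio is not misstated.** A reader might infer that simple randomisation contradicts 1:1, because 6:6 occurs in only 22.6% of draws. The protocol does not support that reading: 1:1 ordinarily means equal probability for each site. Every realised split is a valid, unbiased allocation.
- **Missing 6:6 is not the harm.** An exact split is missed 77.4% of the time, but half of those misses are 5:7, at about 3% in variance. In 61% of draws (2508 / 4096) the loss is nil or trivial. The case rests on 4:8 or worse.
- **The variance factors are conditional.** The protocol gives no site sizes, invitation volumes or intracluster correlation. With very unequal sites the factors would differ.
- **Equal site counts do not balance invited patients.** A reader might expect a forced 6:6 to stop one large site dominating an arm. It would not. Only stratification by volume addresses that, and only in part.
- **Timing.** The Status and timeline section has recruitment starting in February 2021 and due to end in February 2022, with the current version dated 13 December 2021. The infographic goes out with the invitation materials, so many sites may already be allocated. That is an inference, since no SWAT allocation dates are given.
- **Reach.** This is an embedded methodological study. Nothing here affects the BASIL+ primary outcome, its sample size of 392 or the allocation of participants, which is already blocked and stratified.

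These points reduce the finding to an efficiency improvement. They do not remove it: the protocol does fix an unrestricted draw, and the tail probabilities are not small.

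**Conclusion.** The concern holds as a design improvement, not as an error. Simple randomisation of 12 sites carries a 39% chance of 4:8 or worse and a 15% chance of 3:9 or worse. The variance of the SWAT comparison rises by 12.5% and 33% at those two splits, and by about 12% on average. The probabilities are exact for 12 sites and change with the final number. The variance figures assume similar-sized sites and dominant between-site variation. The consequence is confined to the precision of the SWAT, and its practical weight depends on how many sites remain to be allocated.

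**What to change.** In the SWAT section, replace simple randomisation with restricted randomisation of sites:

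- If all sites are known at the outset, draw half of them at random for the infographic arm.
- If sites open in sequence, use permuted blocks. With an odd number of sites or an incomplete last block, the split will be near-even rather than exact.
- Keep generation of the list with the same independent statistician.

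Stratifying by expected invitation volume is optional. It is worthwhile only if volume forecasts exist for each site before allocation. It can leave incomplete blocks, and the stratum should then be carried into an analysis that has only about 12 clusters.

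Apply the change to sites not yet allocated. With few left it will recover little. If all have been allocated, report the realised split and state its effect on the precision of the SWAT comparison.

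**Cost.** A different allocation list, with no extra sites, staff or participants. The last site in a block becomes slightly predictable, but this matters little because sites are to be masked and the sequence is generated independently.
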